## Abstract

**Introduction:**

Diagnosis of endoleaks is imperative to prevent failure of endovascular aneurysm repairs (EVARs). The gold standard for diagnosis of endoleaks is catheter-directed subtraction angiography, which is not a practicable choice for surveillance. CT angiography (CTA) is the historical surveillance modality of choice. Concerns over cost, potential nephrotoxicity of contrast agents and repeated radiation exposure led to colour duplex ultrasound scan (CDUS) becoming an established alternative. CDUS has a lower sensitivity and specificity for endoleaks detection compared to CTA. Contrast-enhanced ultrasound scan (CEUS) represents an improvement of ultrasound imaging but comparisons against CTA report widely varying results, likely due to technical factors of CEUS and limitations of single-phase CTA.

The development of time-resolved CTA (tCTA) offers timing information that much more closely mirrors the dynamic information available from CEUS. Theoretically, these two imaging modalities have the best potential for diagnostic accuracy. The aim of this study will be to compare CEUS to tCTA and investigate the utility of other measurements available from tCTA.

**Methods and analysis:**

This is a prospective, single UK centre, comparative study of paired binary diagnostic imaging modalities. Patients identified in routine post-EVAR surveillance as at risk of having a graft-related endoleak will undergo a CEUS and tCTA on the same day. This will allow the first comparison of CEUS to a semidynamic form of CTA. CEUS sensitivity and specificity to endoleak detection will be calculated.

**Ethics and dissemination:**

The study has achieved ethical approval. We hope the results will define the diagnostic accuracy of CEUS in comparison to a semidynamic form of CTA, representing a methodological improvement from previous studies. Results will be submitted for presentation at national and international vascular surgeryandradiology meetings. The full results are planned to be published in a medical journal.

**Trial registration number:**

NCT02688751.

Strengths and limitations of this studyFirst comparison of contrast-enhanced ultrasound to a dynamic form of CT imaging, representing a methodological improvement.Both imaging modalities occur on the same day removing changing findings as a confounding factor.Primary outcome set as type I/III endoleak (most clinically significant) rather than all endoleaks.Appropriately powered but small study.Single-centre study.

## Introduction

### Background and rationale

Endovascular aneurysm repair (EVAR) is the intervention of choice to treat abdominal aortic aneurysms (AAA).^1^ In comparison to open surgical repair, EVAR confers a reduction of mortality lasting into the short to intermediate term.^2^ However, EVAR is associated with complications which sometimes require secondary interventions in order to maintain efficacy of EVAR. This has been recognised since the inception of the technique and confirmed in observational studies as well as randomised controlled trials.^3–6^ Therefore, periodic surveillance imaging is recommended for life following EVAR.^7 8^ The importance of post-EVAR surveillance remains enduring, its value further highlighted by a recently published analysis of 15-year follow-up after EVAR.^2^

The most common complication in EVAR surveillance is an endoleak,^9^ which is ‘persistent blood flow within the aneurysm sac but outside the stent graft’.^10^ Endoleaks are classified based on the source of blood flow,^10^ but can be grouped into stent graft related (types I and III) and type II (non-stent graft related) endoleaks. Stent graft-related endoleaks generally transmit high pressure causing a high risk of aneurysm expansion/rupture (treatment failure).^11 12^ In contrast, type II endoleaks generally run a benign course, particularly in the absence of aneurysm expansion.^12^ With regard to endoleak imaging, high sensitivity of detection and high specificity of characterisation improve diagnostic utility of surveillance, in particular with an emphasis on distinguishing stent graft-related endoleaks from type II endoleaks. Digital subtraction angiography in multiple planes and a high frame rate of acquisition is the gold standard of endoleak imaging; high frame rates to demonstrate endoleak heamodynamics for better characterisation. However, this modality is not tenable to be used as surveillance imaging.

Historically, EVAR surveillance was undertaken using CT angiography (CTA). Arterial phase CT was the most frequently used modality although, selectively or routinely additional phases are used such as unenhanced, venous phase and even delayed phase. Concerns over cost, use of potentially nephrotoxic contrast agent and repeated radiation exposure led to alternative imaging modalities being investigated and implemented in surveillance regimens. Colour duplex ultrasound scan (CDUS) is the most widely used imaging modality currently.^13^ CDUS is reported to have a lower sensitivity and specificity to detect stent graft-related endoleaks compared with CTA.^14^

Contrast-enhanced ultrasound scan (CEUS) has been investigated as an adjunct to CDUS in the hope of improving sensitivity to endoleak detection. CEUS involves intravenous injection of a microbubble contrast which remains in the blood, allowing improved detection of endoleaks, particularly with contrast coherent ultrasound imaging. CEUS also allows continuous (dynamic) or real-time monitoring of the aneurysm and endoleak as the contrast agent arrives into the endoleak. Modern microbubble agents are expired by the respiratory system, thus avoiding nephrotoxicity. A recent review of 30 222 administrations of a CEUS contrast agent demonstrated a low adverse reaction rate of 0.020%.^15^ CEUS also obviates the radiation exposure associated with CTA. 3D acquisition and reconstructions of CEUS scans are possible^16^; however, this development in the technology is currently limited to single phases of acquisition and therefore losses the dynamic information available in standard CEUS.

Systematic review of the diagnostic accuracy of CEUS (in comparison to CTA) in detection of any endoleak revealed variable sensitivity ranging from 67% to 100% and specificity ranging from 79% to 100%.^17^ The value of this review is compromised by heterogeneity of contrast material used and non-reporting of ultrasound imaging technique used, specifically whether colour duplex combined with contrast or harmonic CEUS imaging was used. There are potentially additional reasons for variability in the reporting such as operator dependence, quality of equipment used as well as body habitus of the patient. The consideration that neither CEUS nor single-phase CTA represent gold standard of endoleak diagnosis led to the metanalysis^14 17^ adopting a bivariate model of analysis. This approach does not compensate for the lack of gold standard comparator as it favours any modality producing false positives. Comparison against the gold standard has never been established for either modality.

### Time-resolved CTA

Time-resolved CTA (tCTA) was first described for endoleak detection in 2010^18^. The single arterial phase is replaced by multiple phases in tCTA, which are typically of lower radiation dose, thus offering dynamic observations of endoleaks, such as flow direction and filling speed, while still retaining many of the advantages of CTA (3D reconstruction, etc) which closely mirror the advantages of the multiplanar digital subtraction catheter angiography. The multiple phases of tCTA can be achieved by broad CT detectors and a static patient in the Fowler position^19^ or rapid shuttling of a supine patient through a standard detector.^20 21^ Sufficient amount of measurements regarding filling patterns of endoleaks on tCTA^21^ are now available to be able to replace a standard arterial phase in CTA with a tCTA that is aimed at detecting stent graft-related endoleaks, without increasing radiation exposure for the patient. Now timings and interpretation of tCTA are understood it is timely to do a comparison of CEUS to the improved comparator of tCTA. This overcomes the limitations of previous studies by comparison of CEUS to a (semi)dynamic form of CTA imaging as a gold standard.

## Methods

### Study design

This is a prospective single-centre comparative study of paired diagnostic imaging modalities, designed to comply with the ‘standards for reporting diagnostic accuracy studies’.^22 23^ Participants will be recruited from a city-wide vascular service in the UK. The service is arranged in a hub and spoke configuration locally and regularly accepts tertiary referrals for complications of previous aortic surgery at other centres. EVAR surveillance is predominately undertaken using CDUS and plain radiography.^24^

### Participants

Potential participants are referred to the study by their vascular surgeon when they require a CTA for further investigations of an endoleak following routine EVAR surveillance and meet inclusion criteria (box 1). They are typically patients with a suspicion of a graft-related endoleak or aneurysm expansion on CDUS surveillance. They are then assessed by the study for eligibility based on exclusion criteria (box 2) and approached to participate in the study, if appropriate. Patients are approached by an investigator and those who give their written informed consent to participate will be enrolled in the study.Box 1Inclusion criteriaAged 18 or over.Able to give informed consent.Undergone an endovascular aneurysm repair (EVAR) of infrarenal abdominal aortic aneurysm.Planned for CT angiography of EVAR.
Box 2Exclusion criteriaUnable to receive CT angiography (CTA) contrastAllergy.Insufficient renal function for standard outpatient contrast study (estimated glomerular filtration rate <45).Overactive thyroid gland.Unable to receive contrast-enhanced ultrasound scan contrastPrevious reaction to Sonovue**®** (ultrasound contrast).Allergy to sulphur hexafluoride (used in electrical industry in circuit breakers, switch gears and electrical equipment).Recent acute coronary syndrome or unstable angina, typical angina at rest or frequent or repeated angina/chest pain—all within previous 7 days.Recent coronary intervention.Previous embolisation of artery in region of endovascular aneurysm repair (affects imaging quality).Body mass index >30 (affects imaging quality).

### Test methods

Participants attend and have a CEUS (index test) and tCTA (reference standard) on the same day. This represents a change from standard care for participants who would otherwise have a CEUS and triple phase CTA (non-contrast, arterial (20 s) and delayed venous phase (90 s)) often on separate days. Participants will also be asked a short number of closed questions to assess functional status and cardiac function (online Supplementary material). On completion of the CEUS and tCTA, participants are returned to their referring surgeons, with clinical reports of the studies for ongoing care. The study team follows the participants’ further treatment and investigation until the end of the study.

10.1136/bmjopen-2017-020835.supp1Supplementary file 1

### Contrast-enhanced ultrasound

CEUS is performed in combination with a standard CDUS in our institution. It is reported as a binary test yielding two values: present or absent for each endoleak type. It is conducted by an experienced clinical vascular scientist with extensive involvement in scans for EVAR surveillance. It is performed on a Philips IU22 ultrasound machine (Philips, Amsterdam, Netherlands), using the a 2–5 MHz abdominal curved array probe. Grey-scale images of the aneurysm neck (when possible), iliac seal zones and maximum aneurysm dimensions are obtained and measured in maximum anteroposterior and mediolateral dimensions. Note is made of the echogenicity of thrombus within the aneurysm sac. Using colour flow imaging and spectral Doppler, waveform characteristics and velocities are recorded in the common femoral arteries. The stent graft is interrogated using colour and spectral Doppler to ascertain patency and flow heamodynamics of the neck, main body and both limbs. Any abnormalities in these parameters are reported. Colour Doppler is used to detect any endoleak. If present, its type, point of inflow, point of outflow and flow dynamics (using sectoral Doppler) are reported.

Optimum views of the area of concern are obtained, prior to contrast injection, using appropriate machine set-ups and controls as determined by the operator. Sulphur hexafluoride microbubble contrast (2.4 mL; SonoVue, Bracco, Milan, Italy) is injected followed by 10 mL of sodium chloride 0.9%; the on-screen timer is started at the start of the injection. Flow direction and filling time ideally should be determined and anatomy of the endoleak established by interrogation. Passive elimination of the contrast agent is allowed to occur and the process repeated for a second injection.

CEUS scan will be reported by the performing vascular scientist to the data point recorded in the data collection pro forma (online Supplementary material), in addition to any clinically relevant points. The vascular scientist will be blinded to the concurrent tCTA at the time of reporting, although will be aware of the previous findings on EVAR surveillance.

### Time-resolved CTA

tCTA is performed on a Siemens Definition AS+scanner (Seimens, Munich, Germany), in our institution. Participants are positioned supine with arms raised above their head. The contrast injector is connected to a 20 G (or larger) intravenous catheter in an anterior cubital fossa vein. A standard topogram scan is performed. Unless not required, a non-contrast scan is performed. The maximum length that can be covered for the time resolution required is 27 cm. This is centred over the EVAR stent graft. Abdominal guides are placed at upper aspect of diaphragm and common femoral arteries for venous phase of scan. Abdominal aorta, just proximal to EVAR graft is selected as trigger area for time-resolved phases.

Contrast is injected, using an auto injector, at 4 mL/s for 96 mL. Participants are asked to adopt shallow breaths and not hold their breath. The time-resolved phase is triggered by a Hounsfield unit (HU)>90 in trigger area. Phases occur at 2.5, 5, 7.5, 10, 15, 20 and 25 s following the automatic trigger; these occur in craniocaudual acquisition, except the 5 and 7.5 s phases which occur in a caudocranial direction. The venous phase is taken in full inspiration and is acquired 75 s following the trigger. Tube setting and calculated predicted radiation exposure are presented in table 1.

**Table 1 T1:** Settings and radiation exposure from arterial and time-resolved phases of CT angiography

	Arterial phase (outside study)	Time-resolved phases (inside study)
Tube voltage	120 kV	80 kV
Tube current	230 mA (effective current–scanner automatically varies)	120 mA
Scan l ength	Variable (dependant on body length)	27 cm
Number of Phases	One	Seven
Expected DLP	599.6*	78.9 mGy/cm per phase (552.3 mGy/cm for time-resolved phase)

*Average DLP used for an arterial phase scan in all CT angiography scans in Royal Liverpool Hospital in month of July 2015.

DLP, Dose Length Product.

All tCTA scans will be reported by a single consultant vascular radiologist. This reporter will be blinded to the results of the CEUS and collect data to the pro forma. It will be reported as a binary test yielding two values: present or absent for each type of endoleak.

### Outcome measures

The primary outcome is:The predictive values of CEUS in comparison to tCTA (as comparator) to detect stent graft-related endoleaks.

Secondary outcomes are:Any adverse events during CEUS or tCTA.Predictive values of CEUS in comparison to tCTA to detect type II endoleaks.Predictive values of both tCTA and CEUS in predicting final endoleak diagnosis (following any further investigations).Predictive values of both tCTA and CEUS in predicting need for a secondary intervention.Evaluate the association between CEUS temporal delay (difference between contrast in endograft and contrast in endoleak) and evaluate its ability to improve the differentiation of endoleak type.Evaluate the association between ‘CEUS contrast in endoleak’ to ‘tCTA contrast in endoleak’ and assess potential as predictive tool, for optimum timing of CTA phases.

Analysis plan

Associations will be established/refuted with summary statistics and graphical analysis and appropriate further statistical testing within the framework of logistic regression. If association can be established, then predictive modelling will be undertaken. The agreement between CEUS and tCTA will be evaluated with Kappa statistic.^25^ Sensitivity/specificity will be calculated along with binomial exact 95% CIs and leave-one-out cross-validation. We will also report the positive predictive value and negative predictive value.

The power calculation^26^ showed the required sample size to be 74. This was calculated based on a prevalence of stent graft-related endoleaks of 11% as demonstrated on previous tCTA studies of endoleaks. It was powered to detect a predicted sensitivity of 0.95 with a tolerated CI of ±0.15. The study commenced recruitment in February 2016 and is ongoing.

Monitoring and data

All patients referred to the study are recorded in the screening log. The sponsoring trust will provide governance oversight and annual reports to the ethics committee will provide ethical overview. Radiation exposure of participants will be monitored and reported to the sponsors and approving research ethics committee. No interim analysis is planned.

On completion of the study, all identifiable patient demographics will be removed and anonymised data will be stored to allow for future analysis of unforeseen benefits. During the study, data are stored in a secure manner within the host institutions data management processes. Access is restricted to the investigators and for audit by the sponsor.

Ethics and dissemination

The main ethical consideration is the change of care from CTA to a tCTA; this was felt to be appropriate in the context of informed consent, now it can be performed without increasing radiation exposure. Ethical approval (15/NW/0908) was granted by a National Health Service Research Ethics Committee. On completion of analysis, we expect to publish in a medical journal, along with the anonymised data set and present the findings widely.

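### The primary outcome is worded as predictive values, but the study is sized on sensitivity and the analysis plan treats PPV and NPV as additional

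*Protocol article*

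**What the plan says.** All the main statements stand under Outcome measures in the protocol article, including the analysis paragraphs that follow the outcome list.

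- Primary outcome: "The predictive values of CEUS in comparison to tCTA (as comparator) to detect stent graft-related endoleaks". The type II secondary outcome uses the same term.
- Analysis: "Sensitivity/specificity will be calculated along with binomial exact 95% CIs and leave-one-out cross-validation". The next sentence adds: "We will also report the positive predictive value and negative predictive value".
- Sample size: the calculation "showed the required sample size to be 74". Its inputs are given as "This was calculated based on a prevalence of stent graft-related endoleaks of 11% as demonstrated on previous tCTA studies of endoleaks" and "It was powered to detect a predicted sensitivity of 0.95 with a tolerated CI of ±0.15".

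The abstract (Methods and analysis) says "CEUS sensitivity and specificity to endoleak detection will be calculated". It does not mention predictive values and does not name a primary outcome. On who is studied, the Participants section says "They are typically patients with a suspicion of a graft-related endoleak or aneurysm expansion on CDUS surveillance". The strengths and limitations list describes the study as small but adequately powered.

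**The concern.** PPV and NPV are different quantities from sensitivity and specificity. They condition on the CEUS result rather than on the tCTA result, and they depend directly on how common graft-related endoleak is among those enrolled. A sample size that secures a given precision for sensitivity does not secure it for PPV.

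Two things are at stake. First, the claim of adequate power is not shown for the measure that the outcome list calls primary. Second, the text supports two different headline results from the same 2×2 table. Unless one pair is fixed as primary before the analysis, the choice can be made after both are known.

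**Working it through.** **Inputs.** From Outcome measures: sensitivity Se = 0.95, tolerated half-width d = 0.15, prevalence p = 0.11, N = 74. Specificity Sp is not given for planning, so it is an assumption here: 0.79, 0.90 and 0.95. The Introduction reports 79% to 100% for CEUS against CTA, but for any endoleak. z = 1.96.

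**Step 1: reproduce the plan's figure.** N = z² · Se(1 − Se) / d² / p = 3.8415 × 0.95 × 0.05 / 0.0225 / 0.11 = 8.11 / 0.11 = 73.7, rounded up to 74. The calculation is a precision calculation for sensitivity. Specificity, PPV and NPV do not enter it. It implies 74 × 0.11 ≈ 8 tCTA-positive and 66 tCTA-negative patients.

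**Step 2: precision of PPV at N = 74.** The expected proportion CEUS-positive is q = Se·p + (1 − Sp)(1 − p), and PPV = Se·p / q. The half-width is 1.96 · √[PPV(1 − PPV) / (74q)]. The N needed for ±0.15 is 3.8415 · PPV(1 − PPV) / 0.0225 / q.

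| Sp (assumed) | q | CEUS-positive of 74 | PPV | Half-width at 74 | N for ±0.15 |
|---|---|---|---|---|---|
| 0.79 | 0.2914 | 21.6 | 0.36 | ±0.20 | 135 |
| 0.90 | 0.1935 | 14.3 | 0.54 | ±0.26 | 220 |
| 0.95 | 0.1490 | 11.0 | 0.70 | ±0.27 | 241 |

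These half-widths use the same normal approximation as the plan's own calculation. Exact intervals tell the same story: 7 of 14 gives 0.23 to 0.77, and 7 of 10 gives 0.35 to 0.93. At Sp = 1.00 the expected PPV is 1 and the approximation collapses to zero width. The exact interval for 8 of 8 is 0.63 to 1.00.

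**Step 3: NPV at N = 74.** NPV = Sp(1 − p) / [Sp(1 − p) + (1 − Se)p]. At Sp = 0.90 this is 0.801 / (0.801 + 0.0055) = 0.993. Across the three specificities NPV is about 0.99 with a half-width of about ±0.02, so it is narrow. The reference point matters, though: a test that calls every patient negative has an NPV of 1 − 0.11 = 0.89. A test with Se = 0.50 and Sp = 0.90 (illustrative) reaches 0.801 / (0.801 + 0.055) = 0.94. An observed 59 of 60 has an exact interval of 0.91 to 1.00, which covers most of the span between 0.89 and 1.

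**The case against.** The strongest reply is that the term is loose wording for diagnostic accuracy. The outcome list uses it broadly, including for final diagnosis and for need of a secondary intervention. The stated hope is to define the diagnostic accuracy of CEUS, and all four measures come from one table and are all committed to in advance. This may well be what was meant. It does not settle the matter, because the same section also uses positive and negative predictive value in their technical sense, so a reader cannot tell which meaning the primary outcome carries. If the reply is right, the correction is simply easier. That the article condenses a fuller document does not help either, since the conflict is between statements that the article does make.

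Four stronger readings are tempting, and the documents do not support them.

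- *Three places disagree on what is primary.* The abstract names no primary outcome, and calculating sensitivity and specificity is compatible with the analysis plan. The mismatch lies within Outcome measures.
- *PPV and NPV are both imprecise.* Only PPV is; NPV is about ±0.02. Nor is sensitivity precise by comparison on an exact interval: 7 of 8 gives 0.47 to 1.00, about as wide as 8 of 15 for PPV (0.27 to 0.79). The case for sensitivity as primary is that the study was designed around it, not that it will be estimated better.
- *The protocol carries its PPV and NPV over to routine surveillance.* It makes no such claim. It describes a referred population, in which these values are a legitimate clinical quantity.
- *The sample size is miscalculated.* It reproduces under the formula in step 1.

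**Conclusion.** The point holds as a mismatch between the named primary outcome and the measure that the sample size and the analysis plan are built on. For PPV as primary, 74 patients give an expected half-width of about ±0.20 to ±0.27 instead of ±0.15, and reaching ±0.15 would take about 135 to 241 patients. NPV would be narrow but is hard to read without its 0.89 floor.

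These sizes rest on the documented sensitivity of 0.95 and prevalence of 11%, on an assumed specificity of 0.79 to 0.95, and on the normal approximation. The 11% comes from earlier tCTA studies. If this referred cohort has a different prevalence, both the PPV figures and the NPV floor move. The mismatch itself does not depend on any of these assumptions.

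**What to change.** State the primary outcome as the sensitivity of CEUS for type I/III endoleak against tCTA, the measure on which the study is sized, together with specificity. List PPV and NPV as secondary, labelled as applying to patients referred for CTA after surveillance. Make the same change to the type II secondary outcome.

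Predictive values over a range of prevalences are optional. If given, they should state the assumption that sensitivity and specificity transfer from this sample, which is referred on suspicion and excludes body mass index above 30.

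The cost is protocol wording only. N = 74 is unchanged under the protocol's formula, and no new data are needed. The article reports recruitment as ongoing with no interim analysis planned, so the change can be recorded before the results are analysed.

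### Two secondary outcomes score CEUS and tCTA against later decisions that the two scan reports themselves inform, so the predictive values are partly circular and can favour whichever test is acted on

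*Protocol article*

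**What the plan says.** Protocol article, Outcome measures, lists two secondary outcomes in which both tests are scored against something later than the scans: "Predictive values of both tCTA and CEUS in predicting final endoleak diagnosis (following any further investigations" and "Predictive values of both tCTA and CEUS in predicting need for a secondary intervention".

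Test methods describes what happens between the scans and those outcomes. After imaging, "participants are returned to their referring surgeons, with clinical reports of the studies for ongoing care", and "The study team follows the participants’ further treatment and investigation until the end of the study".

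Blinding is stated for the two readers only. For CEUS: "The vascular scientist will be blinded to the concurrent tCTA at the time of reporting". For tCTA: "This reporter will be blinded to the results of the CEUS and collect data to the pro forma".

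The introductory section on time-resolved CTA describes the study as a "comparison of CEUS to a (semi)dynamic form of CTA imaging as a gold standard".

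**The concern.** A test's accuracy should be judged against an outcome reached without using that test. Here the clinicians managing the patient hold both reports. If a report prompts an intervention, agreement between report and intervention is partly built in. If no further investigation follows the scans, the only new evidence the article describes for a final diagnosis is the two study reports (incorporation bias). Further investigation is optional and ordered with the reports in hand, so those who receive it may be selected on the results (partial verification bias).

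The primary outcome takes tCTA as the comparator and so cannot assess tCTA. The article's introduction says neither modality has been established against the gold standard. These two secondary outcomes are the only listed ones that score tCTA as well as CEUS against a later outcome. A reader could easily take a difference between the tests there as independent evidence that one of them is better.

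**Working it through.** **The plan's own figure.** The sample size rests on a "prevalence of stent graft-related endoleaks of 11" per cent, an expected sensitivity of 0.95 and a tolerated half-width of 0.15. At two-sided 95% confidence:

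- positives needed = 1.96² × 0.95 × 0.05 / 0.15² = 8.11
- N = 8.11 / 0.11 = 73.7, rounded up to 74

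The stated 74 reproduces. It concerns the primary outcome and is not in dispute.

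**Inputs for the illustration.** All are assumptions for these two outcomes. Both tests have true sensitivity 0.85 and specificity 0.90, with errors independent given true status. Prevalence is 0.11, borrowed from the sample-size statement. A share f of final diagnoses copies the tCTA result, unrelated to what the results are, and the remainder is settled correctly and independently.

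**Building blocks.**

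- P(tCTA+) = 0.11 × 0.85 + 0.89 × 0.10 = 0.1825, and the same for CEUS
- P(both+) = 0.11 × 0.85² + 0.89 × 0.10² = 0.0884
- P(diseased and a given test+) = 0.11 × 0.85 = 0.0935

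**Apparent sensitivity.**

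- P(final+) = (1 − f) × 0.11 + f × 0.1825
- tCTA: [(1 − f) × 0.0935 + f × 0.1825] / P(final+)
- CEUS: [(1 − f) × 0.0935 + f × 0.0884] / P(final+)

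| Share copying tCTA | P(final+) | tCTA | CEUS | Gap |
|---|---|---|---|---|
| 0 | 0.1100 | 0.85 | 0.85 | 0 |
| 25% | 0.1281 | 0.1158 / 0.1281 = 0.90 | 0.0922 / 0.1281 = 0.72 | 0.18 |
| 50% | 0.1463 | 0.1380 / 0.1463 = 0.94 | 0.0909 / 0.1463 = 0.62 | 0.32 |
| 100% | 0.1825 | 1.00 | 0.0884 / 0.1825 = 0.48 | 0.52 |

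**Sensitivity to the assumptions.**

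- With better tests (0.90 and 0.95) and 50% copying tCTA, apparent sensitivity is 0.96 for tCTA and 0.75 for CEUS.
- If the copied test is CEUS, the figures swap exactly.
- If the copied diagnoses follow each test equally often, both show 0.81 at 25% and 0.78 at 50%. Neither is favoured, though neither shows its true 0.85.

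**Where the gap comes from.** Subtracting the two numerators leaves f × (0.1825 − 0.0884) = f × P(tCTA+, CEUS−). The gap therefore arises in discordant patients. If every discordant patient were independently verified, two equally sensitive tests would show no gap. This is why verification has to be reported by result cell.

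**The case against.** The best defence is that this is a condensed article. It does not name who assigns the final diagnosis, gives no rule for patients with no further investigation, and does not say which report is acted on. The full protocol could contain adjudication. Participants are typically referred for suspected graft-related endoleak or aneurysm expansion, and surveillance after EVAR is recommended for life, so a negative scan need not end the work-up. No formal head-to-head test of the two modalities on these outcomes is stated, and both outcomes are secondary.

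Much of this stands, and it rules out several stronger readings that a reader might infer:

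- **That the surgeon sets the final diagnosis, or that it is simply the study reading when nothing further is done.** Both are plausible; neither is stated.
- **That the bias must favour tCTA.** Its gold-standard label makes this likely, but surgeons receive both reports.
- **That the artefact would be 100% against 85% sensitivity.** This ignores tCTA false positives. With specificity 0.90, full copying of tCTA gives CEUS 0.48.
- **That both tests would gain a near-perfect negative predictive value.** Without bias it is already 0.89 × 0.90 / 0.8175 = 0.98 under these assumptions, because prevalence is low. Under full copying of tCTA the CEUS value falls to (1 − 2 × 0.1825 + 0.0884) / 0.8175 = 0.88.
- **That about 8 positives (74 × 0.11 = 8.1) underlie these outcomes, so one patient moves sensitivity by 12.5 points.** That count belongs to graft-related endoleaks in the primary outcome. Final diagnosis is not restricted to those types, and no intervention rate is given.

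The defence does not remove the core. The flow of both reports to the treating surgeons is stated, not inferred from silence. Adjudication elsewhere could settle the diagnosis outcome, but the intervention outcome would still follow from care given with both reports in hand.

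**Conclusion.** The concern holds in a limited form. The circularity is a direct reading of the article for secondary intervention and a strong inference for final diagnosis where no further investigation is done. Its size cannot be known from the document, because the share of diagnoses resting on the study scans alone, and the test followed when they disagree, are not given. Under the assumed inputs, a 25% share following tCTA separates two equally accurate tests by 0.18 in sensitivity, and a 50% share by 0.32. The gap is smaller with more accurate tests and disappears if each test is followed equally often or all discordant patients are independently verified. Only these two secondary outcomes are touched, but the change is cheap and alters what can be concluded from them, so it should be made.

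**What to change.** 1. Add one data field for the basis of each final diagnosis: study scans only, or evidence other than the study CEUS and tCTA, such as catheter angiography or operative findings, where these occur in routine care. If the full protocol already has independent adjudication, say so in the outcome definition.
2. Report the proportion verified in each of the four CEUS/tCTA result cells.
3. Report accuracy against final diagnosis separately for independently verified patients, stating that they are selected on the study results. Give best- and worst-case bounds for the unverified. Inverse-probability-of-verification weighting is not advised: with 74 patients and possibly sparsely verified cells, the weights would be unstable or undefined.
4. Report secondary intervention descriptively by result cell, as association with management and not as predictive accuracy of either test.

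The cost is one data field and revised outcome wording, with no added procedures and no change in care. Fewer patients will count as verified, and the intervals will be wider.
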